# LIHNCS - Lugol’s iodine in head and neck cancer surgery: a multicentre, randomised controlled trial assessing the effectiveness of Lugol’s iodine to assist excision of moderate dysplasia, severe dysplasia and carcinoma in situ at mucosal resection margins of oral and oropharyngeal squamous cell carcinoma: study protocol for a randomised controlled trial

**DOI:** 10.1186/1745-6215-14-310

**Published:** 2013-09-24

**Keywords:** Oral cavity, Oropharynx, Squamous cell carcinoma, Lugol’s iodine, Staining, Resection margins

## Abstract

**Background:**

Oral cavity and oropharynx cancer are increasing in incidence worldwide but survival outcomes have not significantly improved over the last three decades. The presence of dysplasia or carcinoma in situ at surgical margins following resection of squamous carcinoma of the mucosal surfaces of the head and neck has been shown to be associated with a higher incidence of local recurrence and reduced survival. While invasive carcinoma in mucosal surfaces can usually be distinguished from adjacent normal mucous membrane, pre-malignant disease is much less readily distinguished at operation. We describe a protocol for a randomised, controlled trial in which we will assess the effectiveness of Lugol’s iodine staining in allowing visualisation and excision of cancer margin dysplasia at time of primary surgery.

**Methods/Design:**

We will recruit 300 patients diagnosed with oral cavity or oropharynx squamous cell carcinoma. All participants will be planned for primary surgery with curative intent. After completion of baseline assessment participants will be randomised into either a standard surgical treatment arm or surgical treatment including Lugol’s iodine staining.

**Discussion:**

This paper describes the rationale and design of a unique trial in head and neck surgical oncology. If margin dysplasia visualisation with Lugol’s iodine allows complete excision of high-risk, pre-cancer mucosa at time of primary surgery, this may lead to a reduction in local recurrence and improved survival.

**Trial registration:**

Current Controlled Trials ISRCTN03712770.

## Background

The presence of dysplasia or carcinoma in situ at surgical margins following resection of carcinoma of the mucosal surfaces of the head and neck, has been shown to be associated with a higher incidence of local recurrence events [1,2].

While invasive carcinoma in mucosal surfaces can usually be distinguished from adjacent normal mucous membrane, pre-malignant disease is much less readily distinguished at operation. The mucosal surfaces of the head and neck are not unique in this respect. Attempts to improve the identification of early carcinoma and intraepithelial neoplastic change using adjunctive techniques are employed in the cervix, large bowel and oesophagus. These include acetic acid topical application, contact endoscopy, auto fluorescence and the use of Lugol’s iodine [3]. None of these has been subject of evaluation in a clinical trial setting in head and neck cancer.

Extensive literature exists regarding the use of Lugol’s iodine, including use as an aid to the identification of neoplasia of the squamous epithelium of the oesophagus. The structure of the mucosal surfaces of the mouth and oropharynx are very similar to the proximal oesophagus and the risk factors for neoplastic transformation at these sites are similar. Lugol’s iodine visualisation of dysplastic mucosa is employed in management of oesophageal disease [4-8]. There is, however, a very limited literature describing the use of Lugol’s iodine in the management of head and neck mucosal neoplasia and there are no reported clinical trials [8-10].

The majority of the oral cavity and oropharynx is covered by stratified, non-keratinising, glycogen-containing squamous epithelium. It is opaque, has multiple (15 to 20) layers of cells and appears pale pink in colour on visual examination. The intermediate and superficial layer cells contain glycogen in their cytoplasm. In contrast, dysplastic and invasive cancer cells contain little or no glycogen. This is thought to be due to the Warburg effect of increased cytosol glycolysis consequent to the genomic chaos seen in the cancer cell.

Iodine is glycophilic and forms tri-iodide molecules within the glycogen polymer spiral. This results in chocolate brown staining of normal non-keratinised oral and oropharyngeal mucosa. Areas of dysplasia and invasive cancer do not take up iodine as they lack glycogen and appear as pale coloured areas.

Heavily keratinised areas of the mouth such as the attached gingivae and hard palate do not avidly take up Lugol’s iodine. Respiratory mucosa also does not contain glycogen and does not stain. Thus detailed head and neck surgical anatomy knowledge is necessary in interpreting the information gained with Lugol’s staining. The major cancer sub-sites within the oral cavity and oropharynx are lined with glycogen containing and therefore Lugol’s iodine staining sites.

The presence of mucous on the surface interferes with the absorption of Lugol’s iodine. This can be minimised by the use of 1.25% carbocisteine solution prior to Lugol’s iodine.

Occasional mild adverse reactions have been reported [11], but our pilot and feasibility studies have shown that the use of mucosal epithelial staining with Lugol’s iodine is a safe technique, which is simply accomplished. With a short period of familiarisation it is readily adopted by experienced surgeons, is inexpensive, and seems likely to be effective. We believe that a trial demonstrating a clear benefit would have a substantial impact on clinical practice worldwide because of the simplicity of the technique and low cost.

## Methods/Design

### Study population

This study is designed as a prospective, multicentre, randomised controlled trial to assess the effectiveness of Lugol’s iodine in assisting excision of moderate dysplasia, severe dysplasia and carcinoma in situ at mucosal resection margins of oral and oropharyngeal squamous cell carcinoma. It fits into the standard practice of care for UK Head and Neck Cancer, and patients who meet the eligibility criteria (Table 1) and provide informed written consent will be enrolled. Detailed information on benefits and risks will be provided to study candidates to fully inform them of the process. Ethics approval has been received from NRES Committee Yorkshire & The Humber-Leeds East (REC reference: 10/H1306/29).

**Table 1 T1:** Eligibility criteria

**Inclusion criteria**	**Exclusion criteria**
Provision of written informed consent	Previous surgery, chemotherapy or radiotherapy for head and neck cancer
Men and women aged >18 years	Allergy to iodine
Histologically proven squamous cell carcinoma of the oral cavity or oropharynx	Distant metastases (positive neck nodes are not an exclusion)
Planned for primary surgical treatment with curative intent	Nasal, nasopharyngeal or occult primary carcinoma
	Previous diagnosis of cancer in the past 5 years (except basal cell carcinoma or carcinoma of the cervix in situ).

### Randomisation and blinding

Patients will be randomly assigned in a 1:1 ratio to the Lugol’s or non-Lugol’s (control) group. Independent randomisation will be via telephone to the Warwick Medical School Clinical Trials Unit (WMSCTU). Computer-generated random permuted blocks will be used; stratification will be by treatment centre/surgeon, tumour site and T-stage. Treatment allocation will not be masked to the surgical team; however, the patient will not be informed of the treatment.

Data monitors, pathologists and external reviewers will be blinded to treatment allocations. The chief investigator, surgeons and other healthcare professionals will be blinded to all results.

The LIHNCS intervention is to be carried out in theatre during surgery.

The trial follows the pathway as shown in Figure 1 below:

**Figure 1 F1:**
[figure not shown]
LIHNCS trial flowchart.

### Trial intervention and control

Patients in the intervention arm will have primary tumour stained with Lugol’s iodine at time of resection in the operating theatre. Those in the control arm will not have Lugol’s staining. All other intraoperative procedures will be the identical between trial and control arms.

The intraoperative standard operating procedure (SOP) covers application of Lugol’s iodine, tumour volume measured by volume displacement, and preparation of resected tumour for histopathology. It must be followed for all trial patients and is supplied below.

### Lugol’s iodine staining technique

Lugol’s Iodine staining to be performed under general anaesthetic using good retraction, light and assistance.

1. Tumour area irrigated with 0.9% saline.

2. Tumour area irrigated with 20 mL Carbocisteine (125 mg/5 mL).

3. Tumour area irrigated with 0.9% saline.

4. Tumour area irrigated with 20 mL of 1% Lugol’s iodine (4 mL elemental iodine/potassium iodide + 16 mL 0.9% saline) allowing a minimum of 30 s for staining to occur before aspirating excess fluid.

5. Tumour area irrigated with 0.9% saline.

6. Staining procedure may be repeated until staining is adequate.

7. Tumour resection planned to include a 1 cm oncologically safe margin and areas of non-stained mucosa where feasible.

Tumour volume to be measured by volume displacement

1. Standard 250 mL laboratory measuring cylinder filled with sufficient 0.9% saline to completely submerge the tumour sample that is to be measured.

2. Resected tumour added and tumour volume determined by volume displacement.

3. Record volume displaced on Surgery CRF form.

Preparation of resected tumour for histopathology

1. Primary specimen to be sutured to an appropriate platform (gamgee or corkboard) to allow appropriate display of resected specimen and accurate margin assessment.

2. Specimen to be sent to pathology as per standard site procedures.

### Assessments

Resected tumour samples will be analysed locally using recruiting site standard protocols. Slides and the accompanying pathology report are then sent to the trial coordinator where they are anonymised before being sent for central pathology review.

As part of a quality assurance process a central pathology review of all samples will be undertaken, performed by the trial pathologist. All external samples will be re-reported according to the Royal College of Pathologists minimum dataset for head and neck carcinoma histopathology.

In addition to this dataset, the central pathologist will report on the incidence of mild and moderate at mucosal resection margins in addition to severe dysplasia and carcinoma in situ. The minimum dataset from primary site pathology reporting will already report severe dysplasia and carcinoma in situ. Samples from the Bradford Teaching Hospitals NHS Foundation Trust will also be reviewed, as the purpose of the quality assurance of a national spread of samples is to standardise all reports against the reviewing pathologist.

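### The central pathologist receives the local report with the slides, so the read that carries the primary endpoint is not independent of the local result, and the blinding claimed for pathologists is not shown to be secured

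*Protocol article*

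**What the plan says.** All places are in the protocol article.

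- **Randomisation and blinding** makes a general claim that does not separate local from central pathologists: "Data monitors, pathologists and external reviewers will be blinded to treatment allocations". The same section leaves the surgeons, who supply the specimen, unmasked: "Treatment allocation will not be masked to the surgical team; however, the patient will not be informed of the treatment".
- **Background** describes what the intervention does to tissue: "This results in chocolate brown staining of normal non-keratinised oral and oropharyngeal mucosa".
- **Lugol's iodine staining technique** ends its histopathology steps with: "Specimen to be sent to pathology as per standard site procedures".
- **Assessments** gives the route to the result. First, "Resected tumour samples will be analysed locally using recruiting site standard protocols". Then, "Slides and the accompanying pathology report are then sent to the trial coordinator where they are anonymised before being sent for central pathology review". The purpose of the second read is put this way: "As part of a quality assurance process a central pathology review of all samples will be undertaken".
- **Assessments** also says that the local minimum dataset covers severe dysplasia and carcinoma in situ, and that the central pathologist adds the mild and moderate grades.
- **Sample size calculation** defines the primary outcome as dysplasia of any grade at the excision margins.

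**The concern.** Grading dysplasia at a margin is a judgement, and it is the only primary outcome. The surgeons know the arm, so the pathology read is the main protection against assessment bias. Two features of the described workflow weaken that protection.

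First, the central reader is given the local report. That report already states the local finding on severe dysplasia and carcinoma in situ, so the central call on those grades can be anchored to it. Any arm-related difference in the local read could then pass into the central one.

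Second, the blinding claim covers pathologists in general, yet no step is described that would keep a local pathologist from recognising a stained specimen.

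If borderline margins were called less often in one arm for either reason, the result would look like a treatment effect.

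**Working it through.** **1. Which read carries the endpoint.** The endpoint needs every grade. The required local dataset supplies severe dysplasia and carcinoma in situ; mild and moderate come from the central review. Only the central read covers the whole endpoint. The same holds if the threshold is taken as moderate or worse, as in the trial title, because moderate is also added centrally. The article labels this read quality assurance and does not name it as the endpoint source.

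**2. What the central reader has.** Slides and local report go to the coordinator, are anonymised, and go on to central review. The article does not say what anonymising removes, or that the central result is recorded before the local report is seen. As written, the read is not independent of the local margin result.

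**3. What secures blinding of local pathologists.** Background says normal mucosa stains brown. The technique section irrigates with saline after staining, submerges the specimen in saline to measure volume, mounts it and sends it by the site's usual route. No step that conceals the arm is stated. Whether colour persists on arrival at the laboratory is not stated either.

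**4. How sensitive the test is (illustration).** The blinding point rests on no figure in the plan. As a check on the formula, the pooled two-proportion calculation for 30% versus 10%, 90% power and two-sided 0.05 gives

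n = [1.960·√(2·0.20·0.80) + 1.282·√(0.30·0.70 + 0.10·0.90)]² / 0.20² = 82 per group,

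as stated. It also gives the stated 144 for 20% versus 7%.

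Inputs:

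- n = 150 per arm, two-sided 0.05, and margin rates p of 17%, 20% and 30%, all from Sample size calculation.
- Assumed: no true effect, and a share u of positive margins missed in the Lugol's arm only, with u = 10%, 20% or 30%. The documents give no value for u.

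Formulas: q = p(1 − u); d = p − q; m = (p + q)/2; SE0 = √[2m(1 − m)/n]; SE1 = √{[p(1 − p) + q(1 − q)]/n}.

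P(reject) = Φ[(d − 1.96·SE0)/SE1] + Φ[(−d − 1.96·SE0)/SE1].

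Example, p = 0.20 and u = 0.20: q = 0.16, d = 0.04, m = 0.18, SE0 = 0.0444, SE1 = 0.0443. The two terms are Φ(−1.06) = 0.145 and Φ(−2.87) = 0.002, total 0.147.

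| Margin rate p | u = 10% | u = 20% | u = 30% |
|---|---|---|---|
| 17% | 6.8% | 12.9% | 24.1% |
| 20% | 7.3% | 14.7% | 28.2% |
| 30% | 8.9% | 21.5% | 43.2% |

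The nominal rate is 5%.

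**The case against.** A reader might infer that blinding demonstrably fails, because the laboratory receives visibly stained tissue and the report passes that knowledge on. The documents do not support this.

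- Brown staining is described for mucosa in the patient. No text says the colour is still there when the specimen reaches the laboratory, and two contacts with saline come in between.
- The slides and report are anonymised. Nothing says what is removed, so this step may be meant to serve the blinding commitment. The full protocol, not shown, may say so.
- Seeing the local margin result is not the same as knowing the arm. The article promises blinding to allocation, not to the local read, so forwarding the report does not in itself break that promise.
- A reader might also infer that an unblinded local read could serve as the primary endpoint. The required local dataset lacks mild and moderate grades, so it could not supply an any-grade endpoint.
- The error rates presuppose one-directional under-calling in one arm, and nothing in the documents indicates that this occurs.

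All of these stand against the claim that blinding fails. They do not remove the narrower point. Forwarding the local report is a stated procedure, not an omitted detail. It makes the central read dependent on the local one whether or not the arm is revealed, and that dependence biases the comparison if the local read differs by arm.

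**Conclusion.** The point holds in a limited form. As written, the central read, which is the only one required to cover every grade in the primary endpoint, is not independent of the local margin result. The blinding claimed for local pathologists has no stated mechanism behind it. Blinding is not shown to be secured, which is weaker than saying it is broken.

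No figure in the plan changes. Under the assumed 10% to 30% under-calling in the Lugol's arm only, the false-positive rate would be 7% to 28% at a 20% margin rate and 9% to 43% at a 30% rate. These figures show why the read should be protected; they are not an estimate of bias in this trial. The change is worth making because it costs little and protects the sole primary endpoint.

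**What to change.** 1. In Assessments, have the coordinator send the slides under a trial number with a neutral block and orientation key. Withhold the local report, both its findings and any mention of staining, until the central result is locked.
2. Name the locked central read as the source of the primary endpoint instead of describing it only as quality assurance.
3. In Randomisation and blinding, limit the claim to readers for whom blinding is secured. Keep local pathologists in it only if a masking step for them is stated.
4. Restrict any comparison of local and central reads to severe dysplasia and carcinoma in situ, the grades the local dataset requires. A local-read analysis of the any-grade endpoint is not possible from that dataset.

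The cost is a change to the coordinator's dispatch procedure and a few lines of protocol text, with no extra reader. The downside is that sites must supply a block key so that the central pathologist can orient the slides. The article gives the trial as open and recruiting, so the change would protect reads still to be made.

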### Follow-up protocol

The trial duration is expected to take 4 years in total.

Patients will be recruited over a 2-year period and will be followed up for a minimum of 2 years.

Quality of Life (QoL) questionnaires and CRFs will be completed at set time points (Figure 1) when the patient attends for their routine clinic appointments. QoL will be measured using the EORTC QLQ-30 and H&N disease specific EORTC QLQ-35 module questionnaires. Swallowing-related QoL will be measured using the MD Anderson Dysphagia Inventory (MDADI) questionnaire.

It is possible that since more tumours are likely to be removed in the Lugol’s iodine arm, there may be an effect on functionality and quality of life.

At each time point, each domain of each questionnaire will be compared between groups by ACNOVA, that is, linear regression with the follow-up score as the dependent variable, group as the predictor and baseline score as the covariate. Differences between groups will be calculated along with 95% confidence intervals (CI) and *P* values.

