	**Secondary outcome measures:**
1.	Acceptability of the technique to surgeons carrying out surgery for oral and oropharyngeal carcinoma.
2.	Effect of Lugol’s technique on any further treatment carried out (radiotherapy, chemoradiotherapy or further surgery).
3.	Estimate of the two-year locoregional recurrence rates in each group.
4.	Mean and range of volume of tissue removed by each method.
5.	Safety of the technique.
6.	Assessment of quality of life changes using EORTC QLQ-30 and EORTC-35 H&N questionnaires, and the MD Anderson Dysphagia Inventory (MDADI) questionnaire
7.	Overall survival

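### Quality of life is to be tested by a separate baseline-only ANCOVA with a P value for every domain at every time point; one repeated-measures model per domain and a single key P value would serve better

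*Protocol article*

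**What the plan says.** The protocol article's Follow-up protocol section names three instruments. On general and disease-specific quality of life: "QoL will be measured using the EORTC QLQ-30 and H&N disease specific EORTC QLQ-35 module questionnaires". On swallowing: "Swallowing-related QoL will be measured using the MD Anderson Dysphagia Inventory (MDADI) questionnaire". They are completed at routine clinic visits, on a schedule given in Figure 1, which is not shown.

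The analysis is fixed in the same section: "At each time point, each domain of each questionnaire will be compared between groups by ACNOVA". The model is "linear regression with the follow-up score as the dependent variable, group as the predictor and baseline score as the covariate". The output is also fixed: "Differences between groups will be calculated along with 95% confidence intervals (CI) and *P* values".

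Quality of life is item 6 of the seven secondary outcomes in Table 2. The Follow-up protocol section also says why it matters here: the Lugol's arm may have more removed at surgery, which could affect function and quality of life.

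The Randomisation and blinding section stratifies by T-stage, tumour site and centre or surgeon. None of these appears in the quality-of-life model.

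**The concern.** This is a stated method, not a gap left to the analysis plan. A team following the text would produce one P value for each combination of domain and visit, with nothing in the text to say which of them counts. Quality of life is where the plan itself foresees a possible adverse effect of the intervention. A long list of unranked P values makes it easy to promote a chance difference or to dismiss a real one as chance.

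The second issue is the model. A regression at a single visit takes no information from the same patient's other visits. Follow-up lasts at least 2 years in patients for whom recurrence and death are themselves outcomes, so some missed questionnaires are to be expected, although the article gives no rate.

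**Working it through.** **Is there a plan figure to reproduce?** None on this point. The article gives no test count, significance level, sample size or completion rate for quality of life. The two-sided 0.05 in the Sample size calculation section is set for the primary endpoint; carrying it over to quality of life is an assumption.

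**Inputs**
- Structure: one test per domain per time point, with a P value each (Follow-up protocol).
- Domains in total, d: not stated. Assumed 20 to 40; smaller values are shown for sensitivity.
- Follow-up time points, v: in Figure 1, not shown. Assumed 3 to 6.
- Level per test: 0.05, assumed.

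**Formulas**
- Tests: k = d × v.
- Expected false positives under no effect: 0.05 × k, whatever the correlation between tests.
- Chance of at least one, independent tests: 1 − 0.95^k.
- Chance of at least one, correlated tests: simulation of equicorrelated normal test statistics, 100,000 runs, counting |z| > 1.96.

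**Results**

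| d × v | Tests | Expected false positives | At least one, independent | At least one, correlation 0.5 |
|---|---|---|---|---|
| 3 × 3 | 9 | 0.45 | 37% | 27% |
| 10 × 3 | 30 | 1.5 | 79% | not run |
| 20 × 3 | 60 | 3 | 95% | 66% |
| 30 × 4 | 120 | 6 | over 99% | 82% |
| 40 × 6 | 240 | 12 | over 99% | not run |

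For 60 tests, 1 − 0.95^60 = 0.954. In the simulation this falls to 85% at correlation 0.3, 66% at 0.5 and 43% at 0.7. With one domain per questionnaire, the expected count stays below 1 even at six visits (3 × 6 = 18 tests; 0.05 × 18 = 0.9).

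**After the change.** One key scale at one visit leaves one test and 0.05 expected false positives. One key domain per questionnaire at one visit would leave three tests, 0.15 expected, and 1 − 0.95^3 = 14.3% for at least one if independent.

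**The model.** The stated regression has two predictors, group and baseline score.
- Without imputation, it can use only patients who have both a baseline score and a score at that visit.
- If missingness depends only on arm and baseline score, the baseline-adjusted comparison at that visit is not biased by it.
- If missingness also depends on earlier follow-up scores, the visit-by-visit regression can be biased. A repeated-measures model that includes those scores is valid under the wider missing-at-random condition.
- Leaving out the stratification factors costs precision; it does not bias the comparison.

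**The case against.** Baseline-adjusted ANCOVA at each visit is a standard, valid analysis. Quality of life is one of seven secondary outcomes and no decision hangs on it. Every P value comes with a difference and a 95% CI. Nothing in the article says that all the P values carry equal weight, and an analysis plan could name a key scale without contradicting it. Multiplicity rules and missing-data handling are commonly left to that plan, so their absence is no finding. The test counts rest on numbers that the article does not show. A mixed model still gives domain-by-visit contrasts, relies on missing-at-random and does not resolve loss through death.

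Most of this stands as a limit on the point. It does not remove it, because the separate tests, the P value for each and the two-predictor model are all written down.

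Three stronger readings are tempting and not supported:
- **That the plan specifies a complete-case analysis from which deteriorating patients drop out.** The article does not say so. It gives no attrition, completion or death rate and does not exclude imputation. Using only patients with both scores is the default behaviour of the stated regression, not a declared rule.
- **That at least one false positive is nearly certain.** The 95% figure needs independent tests, which is unrealistic for related domains measured repeatedly in the same patients.
- **That a real swallowing deficit could not be told from noise.** Swallowing has its own instrument, and the planned CIs allow size, precision and consistency over visits to be read.

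**Conclusion.** The point holds as a minor improvement. The article fixes a separate test with a P value for every domain of three questionnaires at every time point. On the assumed 20 to 40 domains, 3 to 6 visits and level 0.05, that means 60 to 240 tests and 3 to 12 expected false positives if there is no effect. These counts are conditional on numbers not shown and would be smaller with fewer domains or visits. For 60 tests, the chance of at least one false positive is about 95% under independence and about 66% at correlation 0.5.

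The stated model also leaves out each patient's other follow-up scores and the stratification factors. Bias at later visits is possible if missingness depends on earlier follow-up scores; the article does not allow its size, or even its presence, to be established. The primary endpoint's error rate and sample size are untouched.

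**What to change.** Replace the visit-by-visit ANCOVAs with one mixed model for repeated measures per domain. Include arm, visit, arm-by-visit interaction, baseline score and the stratification factors (T-stage, tumour site, centre or surgeon). Take the visit-specific differences and 95% CIs from that model.

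Keep a P value for one key scale and visit named before the data are seen, for example an MDADI score at a stated visit, since swallowing already has a dedicated instrument. Report all other domains and visits as estimates with 95% CIs. State that contrasts at visits after deaths have occurred are among survivors.

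The cost is analysis-plan wording and modest programming, with no new data, visits or patients. The downsides are a missing-at-random assumption that must be stated and defended, and fewer P values to quote for individual domains. Patients without a baseline score would still fall outside this model unless the plan says how they are handled.
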